## Abstract

**Background:**

In case of untreatable suffering at the end of life, palliative sedation may be chosen to assure comfort by reducing the patient’s level of consciousness. An important question here is whether such sedated patients are completely free of pain. Because these patients cannot communicate anymore, caregivers have to rely on observation to assess the patient’s comfort. Recently however, more sophisticated techniques from the neurosciences have shown that sometimes consciousness and pain are undetectable with these traditional behavioral methods. The aim of this study is to better understand how unconscious palliative sedated patients experience the last days of their life and to find out if they are really free of pain.

**Methods:**

In this study we will observe 40 patients starting with initiation of palliative sedation until death. Assessment of comfort based on behavioral observations will be related with the results from a NeuroSense monitor, an EEG-based monitor used for evaluation of the adequacy of anesthesia and sedation in the operating room and an ECG-based Analgesia Nociception Index (ANI) monitor, which informs about comfort or discomfort condition, based on the parasympathetic tone. An innovative and challenging aspect of this study is its qualitative approach; “objective” and “subjective” data will be linked to achieve a holistic understanding of the study topic. The following data will be collected: assessment of pain/comfort by the patients themselves (if possible) by scoring a Visual Analogue Scale (VAS); brain function monitoring; monitoring of parasympathetic tone; caregivers’ assessment (pain, awareness, communication); relatives’ perception of the quality of the dying process; assessment by 2 trained investigators using observational scales; video and audio registration.

**Discussion:**

Measuring pain and awareness in non-communicative dying patients is both technically and ethically challenging. ANI and EEG have shown to be promising technologies to detect pain that otherwise cannot be detected with the “traditional” methods. Although these technologies have the potential to provide objective quantifiable indicators for distress and awareness in non-communicative patients, strikingly they have not yet been used to check whether the current assessments for non-communicative patients are reliable.

**Trial registration:**

The study is registered on ClinicalTrials.gov (Identifier: NCT03273244; registration date: 7.9.2017).

## Background

Once death is imminent, a major concern of family members and caregivers is to assure maximal comfort for the patient during this terminal phase. This can often be achieved by ‘conventional’ pharmacological drugs such as opiates or other symptom-controlling drugs. However, when symptoms are refractory or very severe, e.g. suffocation, a more drastic option may be chosen, known as palliative sedation, terminal sedation or continuous deep sedation (CDS). In such cases comfort is sought by reducing the patient’s level of consciousness [1]. Notwithstanding palliative sedation is ethically controversial, this practice has substantially increased in hospitals, nursing homes and in the home setting. The overall reported incidences vary between 8% and 17% of all deaths [2–5]. Although CDS is more often used in palliative care settings, it is also applied in other populations such as coma patients and the demented elderly.

It is assumed that patients who are sedated according to current standards of care and the guidelines of CDS are unaware of their clinical situation and therefore do not experience symptoms of discomfort such as dyspnea, delirium, and other distressing conditions that are common during the terminal phase. However, a critical evaluation based on more recent evidence raises the question whether the current assessments of suffering and awareness are accurate. Three kinds of problems (assessment of (dis)comfort, the notion of (un)awareness, and titration of drugs) can be discerned.

### Problems with assessment of (dis)comfort in dying patients

The gold standard for detecting distress is patient self-reporting and several instruments, such as the Visual Analog Scale (VAS) or the Numeric Rating Scale (NRS) for pain, are based on this [6]. However, in the case of CDS, patients are unable to communicate whether or not they are still in distress or still (partially) aware of what is going on with them. Some scales have been developed for non-communicative patients as well, but several problems with those have been reported. One well-documented problem is that such scales seem unable to detect pain and awareness in all patients, e.g. because they depend on inferences made from patients’ motor responsiveness, which in case of CDS are nonexistent [7]. Another problem is that these scales are only partially, and in most cases not at all, validated for dying patients [8–10]. In the guidelines for palliative sedation it is acknowledged that the efficacy and safety of palliative sedation are not sufficiently understood and therefore it has been concluded that “there is no scale available to assess the patient’s comfort during sedation”. These findings cause an even bigger concern considering the evidence that family members of patients, compared with caregivers, often have different perceptions of a patient’s comfort and their quality of dying during CDS. While family members tend to overestimate pain, caregivers often seem to rather underestimate it [11]. Furthermore, interrater reliability among nurses and physicians often seems poor [12].

### Problems with (un)awareness

In recent years, doubts have risen on whether patients labeled ‘unconscious’ really are completely insensate and unaware. Studies in different types of patients and settings that critically reviewed awareness, consistently reported that persons were, in contrast to what was assumed by the caregivers, not always (completely) unaware. For example, several studies have shown that patients diagnosed with a vegetative state (currently also called ‘unresponsive wakefulness syndrome’) did show some (minimal) clinical signs of conscious awareness in about 40% of the cases [13]. In some cases, a purportedly unconscious patient could even reliably generate appropriate EEG responses to two distinct commands and occasionally was even able to establish basic communication with ‘yes’ or ‘no’ answers using functional Magnetic Resonance Imaging (fMRI) [14]. These findings demonstrate that at least a minority of clinically diagnosed unresponsive patients shows some residual cognitive function and conscious awareness and that even skilled caregivers were not able to recognize [13]. Also, patients with locked-in syndrome may be mistakenly considered unconscious as may some (rare) patients during general anesthesia [15]. In contrast to the setting where surgical or intensive care patients are managed, advanced monitoring equipment is usually lacking in palliative or home care settings. Terminal or palliative sedated patients ultimately die and therefore patient self-reporting is missing.

The above findings show that the ‘traditional’ clinical tools and procedures to assess comfort and awareness in dying non-communicative patients have important methodological limitations. It should be noted that the problems with assessments are not to be ascribed to a lack of competence in the caregivers, but are of a much more fundamental nature: the absence of reliable tools. The developers of guidelines are aware of these limitations. Although guidelines refer to some scales, the recent Belgian guideline rightly stresses that “their utility in palliative care is not proven” [16]. The current guidelines for CDS are limited to suggest “a daily visit of the physician” and to “continue attention for possible expressions of discomfort (e.g. facial expressions, movements…)” [3, 16].

### Problems with the titration of drugs

Since the aim of CDS is to give optimal comfort, but not to hasten death, the principle of ‘proportionality’ is a pivotal aspect of this treatment and hence the guidelines state that sedation should be ‘no deeper than necessary to avoid suffering’ [1, 16]. To meet this principle of proportionality, caregivers administer the doses of the drugs so that they are high enough to provide comfort but should not hasten death. Studies have shown that CDS does not usually affect survival time [17]. However, as palliative sedation is considered ‘slow euthanasia’ by some, physicians may be ‘extra careful’ with the use of high doses of sedative medication. Several studies have reported underuse of medicines due to a lack of knowledge, unwarranted beliefs, to avoid the perception of giving ‘excessive’ doses and even because of fear among caregivers of being accused of ‘killing’ the patient [18].

#### How to improve assessments of suffering?

Although measuring pain and awareness in non-communicative dying patients is challenging, it is possible. In recent years functional neuroimaging, like functional Magnetic Resonance Imaging (fMRI) and electroencephalography (EEG), have shown to be promising technologies to detect pain that otherwise cannot be observed or detected with the ‘traditional’ methods [14]. Although these technologies have the potential to provide objective quantifiable indicators for distress and awareness in non-communicative patients and to differentiate several types of discomfort (e.g., pain versus delirium), they have strikingly not yet been used to establish reliability of the current assessments for non-communicative patients. It is remarkable that, given the increasing incidence of CDS, there is so little concern about the possibility that patients may experience an uncomfortable dying phase while being unable to signal their suffering. An assessment tool that would allow clinicians to more accurately determine the appropriate doses of medications would encourage more vigorous symptom management in the dying.

Paradoxically, the inability to report distress might also be aggravated or become complete by the use of drugs that might abolish potential further communication and even facial expressions [19]. Hence, some patients might have subjective phenomenological awareness or suffering with very limited, fluctuating or absent behavioral motor signs of distress [20]. The fact that neuroimaging or electrophysiology recordings have not been used so far to validate the assessment tools for distress in non-communicative patients, even when doubts about these tools have arisen, may be related to the reluctance in palliative and end-of-life care to embarrass patients with high-tech equipments as in most cases, patients have already experienced a long treatment period.

In our view, we therefore urgently need a triangulation of methods by which existing scales, qualitative methods and neuroimaging are combined. Each method has its potential and limitations but combined they can be used to validate the commonly used observational scales. The COMPAS (COMfort in PAlliative Sedation) study protocol seeks to address this. As part of the grant application process by the Research Foundation - Flanders (FWO), the study design has been scientifically peer reviewed.

##### Aims of the study

To better understand how unconscious palliative sedated patients experience the last days of their life.To find out if they are really free of pain.To evaluate to what degree assessments of comfort based on behavioral observations are in line with the results from a brain function monitor and a ANI-monitor (analgesia nociception index).Additionally we want to find out if changes in the measured depth of sedation can be experienced by the patient, caregivers and relatives, especially in the last moments of life when sometimes unexpected changes have been measured.

##### Research questions

Are sedated non-communicative dying patients free of pain and other kinds of discomfort?Do the findings of the different assessment methods correspond to each other? In casu:The commonly used assessments (observational scales)The perceptions of family membersThe neurophysiological measurementsAre there differences according to the setting? In casu:Homes for the elderlyHospitals (with Palliative Care Units (PCU) and/or Intensive Care Units (ICU))What is the effect of contextual factors:Medical and pharmacological factors (diseases, medical condition, feeding, medication, etc.).Environmental factors (e.g. the presence of next of kin, noises etc.)

If one or more observational scales provide conclusive results that correspond to the results of the EEG and/or ANI measurement, this can be considered validation. In that case it would seem that observational scales can be reliably used in the palliative population. If not, then we may need to rethink our ways of measuring comfort in dying patients.

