### Procedures

For this prospective study methods from social sciences (qualitative data collection based on interviews, observation), quantitative assessments (scales to assess awareness and discomfort) and neurophysiological data will be combined. Hence, a combination of methods that can be considered fairly objective (e.g. EEG and physiological parameters) and rather subjective methods (e.g. observations by family members) will be used to assess discomfort and awareness. Therefore, the following data will be collected:

*1. Assessment by caregivers* (physicians and nurses) in the routine manner. As explained above, this can be based either on their ‘experience’ or on tools they routinely use in their practice. Every day all treating physicians and nurses will be asked to fill in a brief questionnaire (3 VAS scales) on the patient’s level of awareness (no awareness- completely aware), comfort (no pain – very severe pain) and ability to communicate (no communication possible - full communication possible). After the patient has deceased, all caregivers will be interviewed and asked to comment on their assessments.

*2. Family members’ perception* of the quality of the dying process, their opinion about the patient’s comfort and awareness and their impression of whether they had any kind of (non-verbal) contact with the patient. Parallel with the above described procedure, family members will also be asked to fill in the same 3 VAS scales. Semi-structured interviews will be conducted before and after the patient has deceased.

*3. Assessment by 2 trained investigators* using 1 scale that is mentioned in the Flemish palliative sedation guideline and 3 other scales that have been proposed in the literature [16]:3.1CCPOT (Critical Care Pain Observational Tool), a tool specifically developed for use in patients with limited consciousness [8].3.2RASS (Richmond Agitation-Sedation Scale) [21].3.3M-ESAS (Modified Edmonton Symptom Assessment Scale, validated for a Flemish Palliative Care Population) [22].3.4BPS-NI (Behavioral Pain Scale Non-Intubated) [23].

*4. Neurophysiological assessments* of distress and level of awareness using fMRI has been successfully used to detect awareness and distress that could not be detected by thorough behavioral assessment [10, 13, 14, 24, 25]. Issues of availability and extra stress incurred by patients when transferred are making the use of fMRI for practical and ethical reasons not feasible.

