EEG has recently been shown to provide a feasible and methodologically sound alternative for bedside detection of awareness and pain [26–28]. Although results from these methods need to be interpreted with caution, they can provide important indicators that are especially valuable for assessments in non-communicative patients. Data will be collected with a Neurosense monitor that can easily be used and set up. It displays two frontal EEG signals, and calculates a number of parameters including the bilateral WAVcns index (Wavelet Anesthetic Value for Central Nervous System), ranging from 100 (awake) to 0 (flat EEG). The lower the index, the lower the likelihood of consciousness. The recommended WAVcns for general anesthesia with low probability of consciousness is between 60 and 40. For technical details on the respective measurements of awareness and distress we refer to Schulz E et al. and Cruse D et al. [24, 29].

Additionally, heart rate variability (HRV) will be measured using an ANI monitor. HRV is the variation in time intervals between heartbeats and reflects the effect of the vagus nerve on the heart, which is inhibited during pain. It has already been widely studied in relationship to pain, and seems to be a promising biomarker [30]. However, studies with palliative sedated patients show contradicting results thus far [31, 32]. A promising non-invasive technique is the continuous monitoring of HRV transformed into an analgesia nociception index (ANI, 0–100), which assesses parasympathetic activity as a possible measure of nociception [33]. The ANI provides greater stability than raw indices of HRV. A recent study showed that ANI is effective in detecting pain in deeply sedated critically ill patients [34]. The analgesia nociception index is a non-invasive tool based on the analysis of the respiratory fluctuations of heart rate that mainly reflect the variability in the parasympathetic tone. The NeuroSense and ANI monitor record the EEG and ECG signal continuously, enabling a quantitative assessment of these parameters. The data can be used to assess the level of sedation but also to register negative and positive emotion-related activities such as the voice of loved ones and distress.

*5. Observation* of the patient to detect e.g. restlessness, movements etc. To assure a more precise and reliable observation, video and audio registrations will be made of the patient.

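### The validation rule lets agreement of any one scale with either monitor, even a sedation match alone, vouch for observational scales of comfort in general

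*Protocol article*

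**What the plan says.** The rule stands in the Protocol article, Research questions. Its condition is "If one or more observational scales provide conclusive results that correspond to the results of the EEG and/or ANI measurement"; if that is met, "this can be considered validation". The inference drawn is general: "In that case it would seem that observational scales can be reliably used in the palliative population". If the condition fails, the article says that the way comfort is measured in dying patients may need rethinking.

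Procedures, item 3, has two trained investigators score the patient "using 1 scale that is mentioned in the Flemish palliative sedation guideline and 3 other scales that have been proposed in the literature". The four are CCPOT, RASS, M-ESAS and BPS-NI. Procedures, item 4, describes two monitors. The NeuroSense yields the WAVcns index, interpreted as follows: "The lower the index, the lower the likelihood of consciousness". The ANI is introduced as an index "which assesses parasympathetic activity as a possible measure of nociception".

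The only numerical criterion is under Sample size. The correlation of WAVcns with the VAS must be significantly above 0.30, with close to 80% power if the true value is 0.45. That section presents it as a test of a measure of sedation. The VAS is not one of the four investigator scales, and ANI does not appear there.

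**The concern.** The rule has two weaknesses.

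First, it ignores what each instrument measures. The aims are freedom from pain and the soundness of comfort assessment. A match between a sedation scale and a consciousness index answers a different question, yet it meets the condition, and the conclusion then extends to the pain scales.

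Second, it takes the best of several comparisons. One agreement outweighs seven failures, so the chance that some pairing passes when none truly exceeds the required level is greater than for one pairing fixed in advance.

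At stake is the study's main practical message: whether clinicians may rely on observational scales in patients who cannot report pain.

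**Working it through.** **Step 1: count the routes.** Four scales (Procedures, item 3) times two monitors (Procedures, item 4) gives 4 × 2 = 8 pairings. The wording of the condition makes any one of them sufficient.

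**Step 2: set the constructs side by side.** Scale constructs are taken from the names in Procedures; monitor constructs from the text there.

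| Scale | Construct | With WAVcns (consciousness) | With ANI (nociception) |
|---|---|---|---|
| CCPOT | pain | crosses | matches |
| BPS-NI | pain | crosses | matches |
| RASS | agitation–sedation | matches | crosses |
| M-ESAS | several symptoms | mixed | mixed |

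RASS with WAVcns is a proper match, but for sedation. If it alone agreed, the rule would be met and the conclusion would still read "it would seem that observational scales can be reliably used in the palliative population". This step needs no assumption about thresholds or error levels.

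**Step 3: reproduce the plan's power.** Inputs from Participants and Sample size: 40 patients, about 5 scores each, so n = 200; null 0.30; alternative 0.45. Fisher z:

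power = Φ[(atanh 0.45 − atanh 0.30) × √(n − 3) − z]

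- atanh 0.45 − atanh 0.30 = 0.4847 − 0.3095 = 0.1752
- 0.1752 × √197 = 2.459
- one-sided 5%: Φ(2.459 − 1.645) = 79.2%, which reproduces the stated figure
- two-sided 5%: Φ(2.459 − 1.960) = 69.1%, which does not

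The article states no significance level. One-sided 5% with 200 independent scores is what fits, so it is used below as an assumption.

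**Step 4: illustrate best-of-eight.** Suppose this test were applied to each pairing and every true correlation were exactly 0.30.

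- Independent tests at 5%: 1 − 0.95^8 = 33.7%.
- Independent tests at 2.5%: 1 − 0.975^8 = 18.3%.
- Correlated test statistics at 5% (simulated; correlation 0.3 to 0.9 across scales, 0 to 0.5 across monitors): 29.9% down to 14.9%.
- Simulated scores, 200 independent observations, uncorrelated monitors, scale correlation 0.3, 0.5 and 0.7: 31.6%, 27.8% and 23.2%.

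**Step 5: move off the boundary.** Same test, eight independent pairings, all true correlations 0.20, n = 200:

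- (atanh 0.20 − atanh 0.30) × √197 = −0.1068 × 14.036 = −1.499
- one pairing passes with probability 1 − Φ(1.645 + 1.499) = 0.00083
- any of eight: 1 − (1 − 0.00083)^8 = 0.7%

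With n = 40 the same calculation gives 8.4%. At a true correlation of zero and n = 200 the rate is about 1 in 100 million.

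**Step 6: repeated scores.** If five scores per patient were analysed as independent but had a within-patient correlation of 0.5 (assumed), the boundary rate in simulation rises to 45–61% for scale correlations of 0.7 to 0.3. A single pairing then already passes in about 12–14% of studies.

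**The case against.** The strongest reply is that this is not a confirmatory decision rule. Methods/design calls the study explorative and a multi-case study that does not aim at representativity. The rule is worded cautiously, and Data-analysis rests conclusions on an overall mixed-methods assessment discussed by a multidisciplinary team. Named pairs and multiplicity handling could sit in an analysis plan that is not shown. This softens the point, and a missing multiplicity adjustment is not held against the article here. But the article does state a rule, with a conclusion on each branch, and the positive branch speaks of the palliative population. An explorative aim argues for a narrower conclusion.

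A second reply concerns constructs. The rule says EEG, not WAVcns. Procedures says the monitor calculates several parameters, describes EEG as able to detect pain as well as awareness, and says the recordings can register distress. A reader might infer that EEG agreement can never bear on pain; the article does not support so strong a statement. What stands is that WAVcns, the only EEG index it names and interprets, is interpreted only as likelihood of consciousness.

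A third reply concerns size. A reader might infer that scales unrelated to the monitors would be validated by chance in one study out of three. The documents do not support that. The 0.30 criterion is set only for WAVcns with the VAS, the error level is assumed, and the 34% needs every true correlation to lie exactly at 0.30. Step 5 shows how quickly it falls. This reply stands in full.

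**Conclusion.** The point holds as a fault in a stated rule. Agreement of any one of four scales with either monitor counts as validation and is extended to observational scales in general. A sedation match alone would therefore support a claim about comfort. That follows from the text with no numerical assumption.

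Best-of-eight selection raises the chance of a false validation. The direction is certain; the size is illustrative. It is up to 34% with independent tests and about 15–30% with correlated scales, given an assumed one-sided 5% test against 0.30 and all true correlations at 0.30. It is under 1% if they are 0.20 with 200 independent scores. The figure of 200 is also borrowed: it describes relatives' VAS scores, and the investigators who score the four scales will do so more often.

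**What to change.** Replace the rule under Research questions with construct-matched pairs, named before scale and monitor data are linked:

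- Awareness or sedation: RASS with WAVcns.
- Pain or comfort: one named pain scale, such as CCPOT, with ANI.

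State the expected sign. Procedures says the vagal effect on the heart is inhibited during pain, so ANI should fall as a pain score rises. Either reverse ANI or set the criterion in the negative direction; otherwise a lower confidence limit required to exceed a positive threshold would fail a perfectly agreeing pair. Set the threshold for each pair, and use confidence limits that account for repeated scores within patients. Limit each conclusion to the scale and construct that agreed, and report every other pairing as exploratory.

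Adjustment across the two pairs is needed only if they feed one joint claim. In that case, the first Holm step (0.05 / 2 = 0.025, one-sided) lowers power at a true correlation of 0.45 from 79.2% to 69.1%, on the plan's assumption of 200 independent scores. Keeping all eight pairings with a Bonferroni level of 0.05 / 8 = 0.00625 would lower it to 48.4%, which is why naming pairs is the cheaper route.

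The change is one of wording, and its main cost is a narrower claim. Allowing for repeated scores will also show less power than 79%: with only 40 independent pairs, the same one-sided 5% test has 28.1%.
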